# Acupuncture paired with herbal medicine for prediabetes: study protocol for a randomized controlled trial

**DOI:** 10.1186/s13063-017-2014-4

**Published:** 2017-06-28

**Keywords:** Prediabetes, Fasting plasma glucose, 2-h plasma glucose level after 75-g oral glucose tolerance test, Glycosylated hemoglobin, Body mass index, Hemorheology, Traditional Chinese medicine, Acupuncture, Herbal medicine, Individualized treatment based on syndrome differentiation

## Abstract

**Background:**

Type-2 diabetes has become a major disease and is known to seriously impair people’s health worldwide. Prediabetes includes impaired fasting glucose (IFG) and impaired glucose tolerance (IGT) and is the most critical period for preventing type-2 diabetes, as it can be identified and reversed. Studies in the past decade have indicated that acupuncture and Chinese herbal medicine may be beneficial for treating prediabetes. However, a randomized controlled trial (RCT) should be conducted to obtain more clinical evidence on this topic.

**Methods/design:**

An RCT will be implemented in this study, using a72-week study period (24 weeks for the intervention and 48 weeks for follow-up). Participants will be recruited from the Fifth Affiliated Hospital of Guangzhou Medical University in China. Eighty participants will be randomized to the treatment group (acupuncture plus herbal medicine and health education) or the control group (health education only), 40 participants in each. People included in this study must have been diagnosed with prediabetes using Western medicine criteria. The endpoint indices include the incidence of diabetes mellitus and the reversion rate. The primary outcome is fasting plasma glucose (FPG) level, 2-h plasma glucose (2-hPG) level after a 75-g oral glucose tolerance test (OGTT), and glycosylated hemoglobin (HbA_1c_) level. Secondary outcomes include the following: Body Mass Index (BMI); hemorheology, including shear rates of whole-blood viscosity and plasma viscosity. Safety indices include hepatic (ALT, AST) and renal function (BUN, Cr) and records of adverse events, including diarrhoea, colds, pharyngitis, and sleep disorders. Quality control will be implemented, including quality control of the laboratory, researchers, participants, investigational drugs, data and documents, occurrence of bias, supervision, among others, according to uniform standard operating procedures (SOPs) which have been established by the Good Clinical Practice (GCP) office of the Fifth Affiliated Hospital of Guangzhou Medical University.

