#### Secondary outcomes

Middle shear rates of whole-blood viscosity (30/S)Low shear rates of whole-blood viscosity (10/S)Low shear rates of whole-blood viscosity (1/S)Plasma viscosity

Hemorheology, including shear rates of whole-blood viscosity and plasma viscosity, will be tested by capillary method by the same researcher.

All the secondary outcomes will be tested on visit 1 (within 1 week before the study), visit 25 (after 24 weeks), and visit 26 (after 48 weeks).

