#### Additional indicators

Body Mass Index (BMI): BMI = weight (kg)/square of height (m^2^). The weight and height of participants will be measured by the same equipment in the Medical Examination Centre of the Fifth Affiliated Hospital of Guangzhou Medical UniversityIncidence of type-2 diabetes mellitus

Calculated using the following formula:$$ \mathrm{Incidence}\ \mathrm{of}\ \mathrm{diabetes}\ \mathrm{mellitus} = \mathrm{Cases}\ \mathrm{of}\ \mathrm{diabetes}\ \mathrm{mellitus}/\mathrm{Total}\ \mathrm{cases}\ \mathrm{of}\ \mathrm{each}\ \mathrm{group} \times 100\% $$
Reversion rates of FBG, 2-hPG after 75-g OGTT, and HbA_1c_ after 48 weeks of follow-up;

Calculated using the following formula:$$ \mathrm{Reversion}\ \mathrm{rate} = \mathrm{Cases}\ \mathrm{o}\mathrm{f}\ \mathrm{blood}\ \mathrm{glucose}\ \mathrm{t}\mathrm{hat}\ \mathrm{have}\ \mathrm{returned}\ \mathrm{t}\mathrm{o}\ \mathrm{normal}/\mathrm{cases}\ \mathrm{o}\mathrm{f}\ \mathrm{each}\ \mathrm{group} \times 100\% $$

BMI will be tested on visit 1 (within 1 week before the study), visit 25 (after 24 weeks), and visit 26 (after 48 weeks).

Incidence of type-2 diabetes mellitus, reversion rates of FBG, 2-hPG after 75-g OGTT, and HbA_1c_ will be calculated only on visit 26 (after 48 weeks).

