#### Statistical analysis method

Student’s *t* test will be used for group comparison (treatment group versus control group) on primary outcomes and secondary outcomes. the chi-square test will be used for comparing the endpoint events (occurrence of type-2 diabetes and blood glucose change to normal).

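### BMI is a secondary outcome in the abstract but an additional indicator in the body, so whether it has an assigned between-arm comparison depends on which section is followed

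*Protocol article*

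**What the plan says.** - **Abstract, Methods/design:** BMI is named as a secondary outcome, ahead of the viscosity measures: "Secondary outcomes include the following: Body Mass Index (BMI); hemorheology".
- **Outcome measures, Secondary outcomes:** the list has four entries, namely whole-blood viscosity at 30/S, at 10/S and at 1/S, and the viscosity of plasma. The method note covers only these: "Hemorheology, including shear rates of whole-blood viscosity and plasma viscosity, will be tested by capillary method by the same researcher". BMI is not mentioned.
- **Outcome measures, Additional indicators:** BMI stands here with the incidence of type-2 diabetes and the reversion rates. Its schedule is given: "BMI will be tested on visit 1 (within 1 week before the study), visit 25 (after 24 weeks), and visit 26 (after 48 weeks".
- **Statistical analysis method:** two tests are named. The first, Student's, "will be used for group comparison (treatment group versus control group) on primary outcomes and secondary outcomes". For the endpoint events, namely onset of type-2 diabetes and return of blood glucose to normal, it is chi-square. No other class of outcome is mentioned.
- **Analysis parameters:** all parameters are to be analysed in SPSS 19.0. No comparison is named.

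**The concern.** One outcome has two ranks in one current document. An article that condenses a fuller protocol may leave things out, but that does not explain two positive statements that disagree.

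The rank matters because the analysis section assigns tests by class of outcome. If BMI is secondary, it has a t test. If it is an additional indicator, nothing is assigned to it. With the status open, BMI could be presented as a secondary outcome or as a supplementary one once its result is known.

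BMI is not incidental here. The Background names overweight or obesity among the modifiable risk factors for type-2 diabetes. Both arms receive an individualized diet and exercise programme, and the Blinding section accepts that participants can hardly be blinded. BMI is measured on the same equipment throughout, whereas the lifestyle diary is filled in by the participants. Readers will want to see it by arm beside the glucose results.

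**Working it through.** The plan gives no figure to reproduce on this point, so the check is a comparison of sections.

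**Step 1. Rank of BMI**

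| Section | Secondary outcomes | Rank of BMI |
|---|---|---|
| Abstract | BMI and hemorheology | secondary |
| Secondary outcomes | four viscosity measures | not listed |
| Additional indicators | (a separate class) | additional indicator |

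The body has 4 secondary outcomes. If the abstract's hemorheology is read as those same four, the abstract's classification has 4 + 1 = 5.

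**Step 2. Test assigned to each class**

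| Class | Assigned test |
|---|---|
| Primary outcomes | t test |
| Secondary outcomes | t test |
| Endpoint events (two, binary) | chi-square test |
| Additional indicators | none named for the class |

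**Step 3. Crossing the two**

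- Under the abstract's rank, BMI is secondary and the t test covers it.
- Under the body's rank, the t test does not reach it. Nor does the chi-square test, which is for two binary events, while BMI is continuous.
- The other additional indicators, diabetes incidence and reversion, correspond in substance to the two endpoint events, so the chi-square test reaches them. BMI is the only additional indicator with no assigned comparison.
- The SPSS sentence names software and closes no gap.

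Under the body's classification, BMI thus has 3 measurement times (visits 1, 25 and 26) and 0 assigned between-arm tests.

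**Step 4. Precision, for context only**

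With 40 per arm and complete data, the 95% half-width for a standardized difference is 1.96 × √(2/40) = 0.44 SD. At the article's expected dropout limit of 15%, 40 × 0.85 = 34 per arm, and 1.96 × √(2/34) = 0.48 SD. The article gives no SD for BMI and no difference of interest, so these figures cannot show whether the comparison would be informative. They have no bearing on the contradiction in rank.

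**The case against.** **The body never compares BMI.** A reader might infer this, but the documents do not support it. The statistical analysis plan is not shown, and the test for a lower-ranked variable is commonly left to it. A missing test alone would be no finding. What stands is the conflicting classification, which no unseen plan can make consistent within this article.

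**The heading may not be a demotion.** Two of the three kinds of item under Additional indicators are tested through the endpoint events, so being listed there does not rule out a planned test. BMI has the same visits as the secondary outcomes, and the keywords place it between the glucose measures and hemorheology. An incomplete secondary list is at least as plausible as a deliberate demotion. That is a fair argument for which way to reconcile the text, but it leaves the reader guessing.

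**A BMI test would show whether a glucose difference is due to TCM or to lifestyle.** This is also tempting and also unsupported. Weight change arises after randomization and could be part of the treatment effect: the Background itself cites acupuncture work on a peptide that increases appetite. A BMI comparison would describe the arms without separating these routes. Nor does the lack of an assigned test prevent BMI from being reported by arm, since its measurement is prespecified.

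**Selective reporting is speculation.** Nothing suggests intent. The point is only that the text leaves the choice open. The harm is limited, because the primary outcomes and endpoint events are unaffected.

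**Conclusion.** The contradiction is real and can be verified from the article alone. BMI is secondary in the abstract and an additional indicator in the body. Because tests are assigned by class, it has an assigned between-arm comparison under the first classification and none under the second.

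The size is small: one continuous outcome of uncertain rank, in a trial of 80. The conclusion assumes that the analysis section means what it says about which classes get the t test. It does not assume that BMI will go unanalysed, that anyone intends to choose its rank later, or that the glucose results cannot be interpreted without it.

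**What to change.** 1. Give BMI one status in the abstract, Secondary outcomes and Additional indicators. Secondary is the simpler choice, since it agrees with the abstract and with the visit schedule of the other secondary outcomes. If it is to remain an additional indicator, correct the abstract instead. Either choice reconciles the text.
2. Whichever status is chosen, state in Statistical analysis method that the arms will be compared on BMI at visits 25 and 26, with the visit 1 value as a covariate. That value is already collected, and adjusting for it should be more precise than the unadjusted t test. How much more depends on the correlation between visits, which the article does not give. The adjustment can be separated from the reconciliation and would set BMI apart from the other continuous outcomes, so the text should say that this is intended.

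The cost is a change of wording in a few places and two extra secondary comparisons, one per visit. No new data are needed.

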### Sample size

Given the difficulty determining an adequate sample size due to the lack of sufficient preliminary studies, we adopted a pilot study design with 40 participants per group, considering the limited research funds.

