#### Exclusion criteria

History of diabetes (except gestational diabetes)Cardiovascular and cerebrovascular events (cerebrovascular accident in past 6 months, history of myocardial infarction or heart failure; severe organic heart disease; aneurysm of a main artery or dissecting aneurysm; specific angina; type II degree atrioventricular block; sick sinus syndrome)Impairment of hepatic or renal function: abnormal alanine aminotransferase (ALT), aspartate aminotransferase (AST), blood urea nitrogen (BUN) or creatinine (Cr)Endocrine disease, such as hyperthyroidism, autoallergic disease, cancer or other serious or potentially fatal illnessPregnancy, preparation for pregnancy or active lactation in womenPatients with mental illness or those who are uncooperativeParticipation in other clinical trial within the last 2 weeksRefusal to provide consent for the study

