#### Safety indices

Alanine aminotransferase (ALT) levelsAspartate aminotransferase (AST) levelsBlood urea nitrogen (BUN) levelsCreatinine (Cr) levels

All the safety indices will be tested on visit 1 (within 1 week before the study) and visit 25 (after 24 weeks).

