#### Criteria for the evaluation of safety

As an adverse reaction could not be the criterion of safety in this trial, the safety of the TCM interventions will be assessed by hepatic and renal function as follows:Safe without any significant changes in hepatic or renal functionRelatively safe with less than 20% changes in hepatic and renal functionTermination of the interventions due to more than 20% changes in hepatic and renal function

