## Discussion

We are expecting to discover that, compared with lifestyle interventions, the comprehensive treatments of TCM can be more helpful for preventing prediabetes eventually developing in to diabetes mellitus. And we are also wondering whether TCM methods would cause the side effects of hepatic and renal function impairment. In this trial, we emphasize the importance of individualized treatment for participants with prediabetes. We have made the following adjustments which are different from ordinary protocols of TCM studies in order to match the goal of both individualized and scientific:For demonstrating the precise hypoglycaemic effects of TCM, objective laboratory examinations including FPG, 2-hPG level after OGTT, and HbA_1c_ will provide the primary outcomesFor individual treatment, the changes in participants’ symptoms will be recorded carefully according to four diagnostic methods of TCM including inspection, listening and smelling, inquiry, and pulse-taking and palpation, and will be considered as the basis for adjusting the components and doses of the formula, rather than AEsFor authenticity, we will use RRMS (http://www.medresman.org/login.aspx) to manage the trial data. The changes in participants’ symptoms will be timely entered into RRMS before their next coming and can be checked publicly by a shared password

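### The safety grades can be read as needing both organs to change and give no direction, so an isolated liver or kidney rise above 20% may fit no grade and falls can count as harm

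*Protocol article*

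**What the plan says.** All of this is in the protocol article.

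- **Abstract, Methods/design:** "Safety indices include hepatic (ALT, AST) and renal function (BUN, Cr) and records of adverse events". This sentence only lists the indices.
- **Criteria for the evaluation of safety:** the section opens "As an adverse reaction could not be the criterion of safety in this trial" and bases the verdict on hepatic and renal function. Grade 1 (safe) requires no significant change in hepatic *or* renal function. Grade 2 (relatively safe) requires changes below 20% in hepatic *and* renal function. Grade 3 (termination of the interventions) applies to changes above 20% in hepatic *and* renal function. No grade names a marker, gives a direction or quantifies a significant change.
- **Safety indices:** "All the safety indices will be tested on visit 1 (within 1 week before the study) and visit 25 (after 24 weeks").
- **Exclusion criteria:** impaired function at entry is excluded, defined as "abnormal alanine aminotransferase (ALT), aspartate aminotransferase (AST), blood urea nitrogen (BUN) or creatinine (Cr").
- **Discussion:** the investigators ask "whether TCM methods would cause the side effects of hepatic and renal function impairment".
- **Sample size:** "we adopted a pilot study design with 40 participants per group, considering the limited research funds".

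**The concern.** Adverse reactions are ruled out as a safety criterion, so these three grades carry the whole verdict. A herbal intervention that affected only the liver, or only the kidney, is an obvious case for such a scheme to catch. Whether it does depends on how one conjunction in grade 3 is read. Without a direction, a drop in ALT or creatinine can also be graded like a rise, although the Discussion asks about impairment.

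The limit is also relative. Everyone is normal at entry on all four tests, so a 20% movement can lie wholly inside the normal range and arise from ordinary within-person variation. Two readers holding the same laboratory data could therefore report different safety results.

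**Working it through.** **1. The plan's own figure.** The 20% limit is stated without a derivation, so there is nothing to reproduce.

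**2. The grades applied to example cases.** Inputs are the percentage change in a hepatic and in a renal marker. The document does not define a significant change; 5% was assumed. That choice sets only the line between grades 1 and 2. A change beyond 20% is taken to be significant.

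| Hepatic / renal change | Both organs needed, any direction | Either organ suffices, any direction | Rises only (both / either) |
|---|---|---|---|
| +10% / 0 | Relatively safe | Relatively safe | Relatively safe / Relatively safe |
| +20% / 0 | no grade | no grade | no grade / no grade |
| +50% / 0 | no grade | Termination | no grade / Termination |
| +200% / 0 (tripling) | no grade | Termination | no grade / Termination |
| 0 / +50% | no grade | Termination | no grade / Termination |
| +30% / +30% | Termination | Termination | Termination / Termination |
| −30% / −30% | Termination | Termination | Safe / Safe |
| −30% / 0 | no grade | Termination | Safe / Safe |

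The gap for single-organ rises above 20% exists only when both organs are needed. The problem with falls exists whenever no direction is set. A change of exactly 20% has no grade under any reading, because grade 2 stops below 20% and grade 3 starts above it.

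**3. How often chance alone crosses 20%.** The documents give no within-person variation. Three CV sets are assumed, in the order ALT / AST / BUN / Cr: (a) 10/10/10/5%, (b) 15/12/12/5%, (c) 20/12/14/5%. Markers are taken as independent, grading as per participant, and true change as nil.

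The log ratio of two readings has SD s = √2 · √ln(1 + CV²). For one marker, p = P(log ratio > ln 1.2) + P(log ratio < ln 0.8).

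- CV 5%: p = 0.006
- CV 10%: s = 0.141, p = 0.098 + 0.057 = 0.155
- CV 12%: p = 0.234
- CV 14%: p = 0.306
- CV 15%: p = 0.339
- CV 20%: s = 0.280, p = 0.257 + 0.213 = 0.470

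Any of four markers: 1 − Π(1 − p).
Both organs: [1 − (1 − p_ALT)(1 − p_AST)] × [1 − (1 − p_BUN)(1 − p_Cr)].

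For set (a), any = 1 − 0.845³ × 0.994 = 0.40, and both = 0.286 × 0.160 = 0.05.

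| CV set | Any marker, either direction | Any marker, rises only | Both organs, either direction |
|---|---|---|---|
| (a) | 0.40 (16 of 40) | 0.27 | 0.05 (2 of 40) |
| (b) | 0.61 (25 of 40) | 0.41 | 0.12 (5 of 40) |
| (c) | 0.72 (29 of 40) | 0.48 | 0.18 (7 of 40) |

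The choice of reading alone changes the expected count by a factor of about 4 (0.72/0.18) to 9 (0.400/0.0457).

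**4. Dependence on independence.** Positive correlation, for example between ALT and AST, lowers the any-marker figure. It cannot fall below the largest single-marker probability: 0.155 in set (a), 0.470 in set (c). Correlation across organs raises the both-organs figure, so the gap between readings would narrow.

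**The case against.** The best defence is that *hepatic and renal function* is simply the article's label for the panel. The same phrase introduces the criteria and recurs in the Discussion. On that reading grade 3 is the complement of grade 2 apart from exactly 20%, and a tripled ALT is caught. This is a fair reading but not the only one, and under it a fall in one organ alone becomes a termination event. The Discussion's reference to impairment suggests that rises were meant; the criteria do not say so.

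Several stronger readings are tempting and not supported:

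- *The switch from or to and is a contradiction between grades 1 and 2.* It is not. Grade 1 is negated, so both grades require both organs to be acceptable. Only grade 3 is ambiguous.
- *Any liver-only rise goes ungraded.* Below 20% it is graded under every reading.
- *The abstract sentence is itself wrong.* It only lists indices and contains no grade, limit or conjunction at issue.
- *The grades mostly measure noise.* That rests on assumed CVs, independent markers and per-participant grading. The article does not say whether the participant or the group is graded.
- *Participants would be wrongly stopped or kept on treatment.* On the scheduled tests this does not follow: the second measurement comes after the 24-week intervention.

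It also stands that no data are lost. All four values are recorded, and serious adverse events are a separate ground for suspension.

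**Conclusion.** The point holds in limited form. The text that fixes the only safety verdict allows two readings of its top grade and sets no direction. If both organs are needed, a single-organ rise above 20% has no grade and falls above 20% in both organs meet termination. If either suffices, the rise is caught but an isolated fall counts as harm. This follows from the wording alone.

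The chance figures (40–72% against 5–18%) show that the reading could matter to the reported result. They depend on CVs and a correlation structure that the documents do not give, and should not be quoted as properties of this trial. The consequence lies mainly in the safety conclusion.

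**What to change.** 1. In *Criteria for the evaluation of safety*, define the termination limit as an increase of 20% or more in any of ALT, AST, BUN or Cr. This settles the conjunction, the direction and the value of exactly 20%, and makes grade 3 the complement of the below-20% limit.
2. For the safety conclusion, report by arm and separately for liver and kidney the number of participants with a visit-25 value above the laboratory's normal range, with exact 95% confidence intervals. The exclusion criteria make everyone normal at entry, so each such value is a new abnormality. The control arm shows the background rate.

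The second step is needed because the reworded limit would still be crossed by chance in 27–48% of participants under the assumptions above. Conversely, the counts miss a rise that stays within the normal range, which the relative limit still records.

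The cost is the wording of one section and one table from measurements already scheduled. The article states that the trial had not started at submission. The price is that a one-word verdict of safe gives way to counts with wide intervals: 0 of 40 has an exact two-sided 95% upper limit of 1 − 0.025^(1/40) = 8.8%.
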